#### Secondary Objectives

The secondary study objectives are (1) to determine the preliminary effects of the intervention on sedentariness, and (2) to develop a novel method of analysis of postural data collected using IMUs in a real-life context.

## Methods

### Study Design

This study protocol, designed according to the CONSORT (Consolidated Standards of Reporting Trials) statement for feasibility trials [25], has a stratified, closed cohort, two-cluster stepped-wedge design with a pragmatic approach. The stepped-wedge design offers an ideal structure that allows for a robust evaluation of an intervention within the bounds of logistical constraints [27]. In addition, this study design allows both clusters to be exposed to the intervention with consideration of the unique context of each cluster.

### Participants

Two primary schools were recruited for participation in the study. Participant classrooms (children aged 10-11 years) will be the unit of randomization and both classrooms (clusters) will be exposed to the intervention but will serve as their own control. All participants in each cluster will be exposed to the intervention from which a sample will be selected to provide baseline and follow-up measurements, and qualitative interviewing. Measurements for each selected participant will be taken at baseline, prior to the onset of intervention implementation, and followed up at the end of the trial period. Baseline measurements and implementation of the intervention in classroom 2 will follow those of classroom 1. This study was granted ethical approval by Stellenbosch University Health Research Ethics Committee (reference number: S17/08/130).

### Study Intervention

The proposed intervention has two components: (1) novel height-adjustable sit-stand desks (KUZE desks; patent reference: A2017/01821), and (2) a series of health educational videos that encourage reduced classroom sedentariness and promote classroom physical activity. Usual classroom furniture will be replaced with KUZE desks after baseline measurements are performed. Prior to the implementation of the intervention, the researcher will train the students and teachers on how to safely and effectively use the KUZE desks. The training will include how to select and adjust the seat and desk height for sitting and standing. When used as a standing desk, the KUZE desk is placed on the existing desk and adjusted to the appropriate height.

During a teacher consultation prior to the onset of the project, the teacher will be shown the playlist of short health education videos provided on a mobile external hard drive. The videos are voiceover animations about the importance of reducing classroom sedentariness, awareness of good sitting posture, and increasing physical activity beyond the classroom. All videos contain an interactive segment of physical activity linked with simple mathematics tasks that the students are encouraged to engage with. The frequency at which the videos should be played will not be prescribed to the teacher. Strategies based on findings from a prior qualitative process that explored the potential barriers and facilitators to implementing a classroom-based intervention in primary school classes will be discussed.

### Setting

This study will be conducted in two primary school classrooms in the Western Cape region of Cape Town, South Africa. The Western Cape is characterized by broad socioeconomic, language, and cultural diversity, which will allow for the feasibility of the intervention to be tested in a resource-constrained environment as well as in an adequately resourced school environment. If the study is deemed to be feasible in a challenging resourced-strained environment, we consider that it will also be feasible in a range of less challenging scenarios.

### Trial Design

This is a school-based, pilot cluster stepped-wedge feasibility trial. Individual students in grade 5 or 6 (10-11 years old) will be the unit of analysis with the classroom as the unit of randomization. Quintiles are socioeconomic categorizations of schools in South Africa that determine the state funding of the school, which is based on income levels, dependency ratios, and literacy rates in the area [28]. Although there will be no need to stratify the randomization of the clusters in this trial as there are only two participant classrooms, it is proposed that stratification by school quintile should be carried out during a future full trial. Baseline physiological data will be measured prior to the start of the intervention. Interviews with teachers and focus group discussions will be conducted after the intervention to assess the feasibility of the study. Figure 1 shows the proposed study design, and Multimedia Appendix 1 provides a SPIRIT diagram [29] for the design and timescales of the feasibility study.

**Figure 1 figure1:**
[figure not shown]
Study design.

### Feasibility Outcomes

Two broad feasibility criteria categories are to be considered: adherence and project pragmatics. The detailed success criteria and indicators are outlined in Table 1.

**Table 1 table1:** Feasibility criteria.

Feasibility criteria	Success indicator	Measurement method
Delivery of the health education videos	The teacher develops a suitable routine of playing the videos and adheres to it	Qualitative feedback at exit interview (at 13weeks)
Acceptance of KUZE as a sit-stand desk	Students and teachers accepted the KUZE as the classroom furniture for the entire study period	Qualitative feedback at exit interview (at 13 weeks)
Compliance with wearing activPAL and IMU^a^ sensors	100% of the subsample selected to be monitored agreed and complied to wearing the sensors during the data collection sessions	Researcher monitoring dropout rate
Usage of the KUZE desk	15% reduction in sitting time, reduction in episodes of prolonged sitting, increase in standing time, increase in sit-to-stand transitions	activPAL
Classroom retention to the study	All classrooms initially recruited remain in the study	Researcher monitoring
Integrity of physical activity and postural dynamism data	The integrity (degree of corrupt data due to technical or human factors) of 80% of all data captured with objective tools	Researcher monitoring

^a^IMU: inertial measurement unit.

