### Study Aims and Objectives

#### Primary Objectives

Adherence and project pragmatics are the two primary feasibility outcomes of interest in this study. Adherence to the intervention refers to the extent to which students and teachers comply with the novel furniture and utilize the health education video curriculum. The pragmatics refer to effectively capturing physical activity and postural dynamism data with activPAL microsensors (PAL Technologies, Glasgow, UK) and Noraxon Myomotion (Noraxon, Scottsdale, USA) inertial measurement units (IMUs), respectively. Several pragmatic factors have been identified that could threaten data loss, such as electromagnetic interference from classroom furniture and building infrastructure, Wi-Fi frequency traffic from wireless-enabled devices in close proximity, and IMU sensor battery performance during multiple days of capturing prolonged trials in excess of 1 hour. To our knowledge, activPAL sensors have not previously been used to measure physical activity in this population in South Africa. This study therefore provides the first opportunity to appraise acceptability of using this technology.

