### Sample Size

A sample size calculation was not performed as per the CONSORT extension statement for feasibility studies [25]. A classroom from a fee-paying and a nonfee-paying school will be recruited. The diversity within the sample is expected to provide a sufficiently broad spectrum of considerations to assess the feasibility of the intervention and the pragmatics of data collection. To limit the impact on the classroom environment, no more than 10 morning data collection sessions per cluster are planned. The availability of only 2 Noraxon systems and 10 activPAL sensors presents a logistical constraint that will only allow for the collection of postural dynamism data and classroom physical activity data from 20 students from each cluster respectively. The sample selected for measuring physiological outcomes will be randomly chosen from the class list. An equal number of males and females of 10 to 11-year-old students will be sampled. The participants in the qualitative study will include students who took part in physiological data collection and those who were only exposed to the intervention but did not provide physiological data.

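### The data-integrity criterion scores only captured data and, read literally, pools activPAL with IMU, so it can be declared met with one of the two measurement systems unusable

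*Protocol article*

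**What the plan says.** In the protocol article, Primary Objectives names project pragmatics as one of two primary feasibility outcomes: "The pragmatics refer to effectively capturing physical activity and postural dynamism data with activPAL microsensors" and, in the same sentence, with Noraxon IMUs. It then lists what could go wrong: "Several pragmatic factors have been identified that could threaten data loss, such as electromagnetic interference from classroom furniture and building infrastructure", Wi-Fi traffic from nearby devices, and "IMU sensor battery performance during multiple days of capturing prolonged trials in excess of 1 hour". For activPAL it raises a different question: "This study therefore provides the first opportunity to appraise acceptability of using this technology".

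Table 1 (Feasibility Outcomes) turns this into one row, headed "Integrity of physical activity and postural dynamism data". Its success indicator is "The integrity (degree of corrupt data due to technical or human factors) of 80% of all data captured with objective tools", and the method is monitoring by the researcher. The row gives no threshold per device, no counting unit and no denominator of planned recordings. The only other sensor row asks that every selected child agree to wear the sensors and do so.

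Under Interpretation of Feasibility Success Criteria, the row is one of six. If all six pass, the project continues to a larger trial. With three or more, the protocol is first modified in minor ways.

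**The concern.** The stated outcome is whether data can be captured, and the stated threat is data loss. The criterion, however, divides by what was captured. A session lost completely is not scored as a failure; it disappears from the calculation.

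The two systems also contribute very different numbers of recordings. activPAL is worn for ten school days by each measured child, while the IMUs are limited by two systems and a cap on mornings. One percentage over both can be carried by the system that records more often.

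The decision to proceed is at stake. Suppose the other five criteria pass. If the integrity row is wrongly scored as met, the count is six of six and the rule says continue. If it is scored as failed, the count is five and the rule says modify first. The wear row does not protect against this, because a child can comply fully while the system records nothing.

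**Working it through.** **Inputs**
- Threshold: 80% of captured data, one row for both devices (Table 1).
- Devices: 2 Noraxon systems and 10 activPAL sensors (Sample Size).
- Sessions: "no more than 10 morning data collection sessions per cluster are planned" (Sample Size).
- activPAL wear: 10 school days per child (Physiological Outcomes).
- Measured students: 20 per cluster (Sample Size); 10 per class measured at baseline so far (Results).
- Assumptions: one child per Noraxon system per session; the session cap applies to each measurement round. Counts are per cluster and round. The ratios are unchanged over 2 clusters and 2 rounds.

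**The plan's own figure first.** IMU: 2 systems × 10 sessions × 1 child = 20 students, which reproduces the stated 20. activPAL: 10 sensors, each worn by one child for 10 days within 10 sessions, gives 10 students and 10 × 10 = 100 student-days. The stated 20 does not follow for activPAL.

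**Test.** Let every activPAL record be valid and every IMU session fail. Criterion = valid records / captured records, met if at least 0.80.

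*Case A: failed IMU sessions leave no file.* By student-day, 100/(100 + 0) = 100%, met. The IMU term is zero in any unit, so this result does not depend on how records are counted.

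*Case B: failed IMU sessions are kept as corrupt files.*

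| Counting unit | Calculation | Result |
|---|---|---|
| Student-day | 100/(100 + 20) | 83.3%, met |
| Hours, assuming 3 h activPAL per day and 3 h per IMU session | 300/(300 + 60) | 83.3%, met |
| Hours, assuming 5 h and 1 h | 500/(500 + 20) | 96.2%, met |
| Student, 10 activPAL and 20 IMU | 10/(10 + 20) | 33.3%, not met |
| Student, 20 and 20 | 20/(20 + 20) | 50.0%, not met |
| IMU sensor, four body sites | 100/(100 + 20 × 4) | 55.6%, not met |

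Break-even in case B: a/(a + i) ≥ 0.80 requires a ≥ 4i, where a is activPAL records and i is IMU records. By student-day the ratio is 100/20 = 5, so the pass is narrow. Five corrupt activPAL student-days would give 95/120 = 79.2%, not met.

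**Partial loss, as an illustration.** If half the scheduled sessions record nothing and the rest are clean, the criterion stands at 100% while the yield is 50%.

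**Which repair is needed**
- Planned denominator, still pooled: 100/120 = 83.3%, still met.
- Split by device, still on captured data: empty IMU sessions still drop out. If 10 of 20 record nothing and 10 are clean, the result is 10/10 = 100%.
- Both changes: IMU 0/20 = 0%, not met. A pass needs 0.80 × 20 = 16 IMU sessions and 0.80 × 100 = 80 activPAL student-days.

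**The case against.** The strongest reply is that pooling is a reading and not a stated rule. The cell never says that one combined percentage is computed, and 80% for each data type may have been meant. That is possible, but the text refers to all captured data and gives no threshold per device. A per-device reading would also leave the denominator problem in place.

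Second, many failures would be visible. A battery that dies partway leaves a truncated file, and interference can corrupt a recording without erasing it. Such files are captured and would be scored. This stands: only sessions with no file escape entirely. For the others, the answer depends on the counting unit, and Trial Design names the student as the unit of analysis, under which total IMU corruption fails the criterion.

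Third, total IMU failure would hardly go unnoticed. It would defeat the secondary objective of developing an IMU analysis method, and feasibility results are to be reported narratively. This also stands, but the six-criterion rule works from the formal scores.

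Some stronger readings are tempting and not supported:
- A reader might infer a comfortable pass of 91%, from 200/220 or 100/110. The first needs 20 children for 10 activPAL days each, which 10 sensors and at most 10 sessions do not allow. The second uses only half of the 20 IMU slots.
- A reader might infer that IMU failure is the main technical risk. The Primary Objectives do not rank the risks, and only battery performance is tied to the IMU by name.
- A reader might take the gloss on integrity literally, as a demand for 80% corrupt data. The row title and column heading make the intent clear, so this is a wording slip.
- A reader might infer that the criterion passes whenever the IMUs fail. It does not, as the counts by student and by sensor show.

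Finally, an article may leave counting rules to the full protocol. That covers missing detail, but here the article itself states the denominator.

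**Conclusion.** The concern holds in limited form. On the literal pooled wording, complete non-recording by the IMUs with clean activPAL data scores 100% in any counting unit; this needs no numerical assumption. If failed sessions survive as corrupt files, the result is undetermined: 83.3% by student-day (met), 33.3% to 50% by student and about 56% by IMU sensor (not met). The student-day figure rests on 10 activPAL sensors for 10 days, 2 IMU systems for 10 sessions and one child per system per session. By data volume nothing can be said, because no sampling rates are given.

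The criterion can therefore return a pass with one of two measurement systems unusable, for a primary feasibility outcome that feeds the decision to proceed. It should be corrected before the criterion is scored. The documents do not show that such a failure is likely, or that the pass would be comfortable.

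**What to change.** Restate the Table 1 indicator as: *at least 80% of scheduled student-sessions yield usable (non-corrupt) data, assessed separately for activPAL and for IMU; a scheduled session that recorded nothing counts as a failure.* Both the scheduled denominator and the split by device are needed. Tabulate causes of failure (interference, wireless traffic, battery, human error) and report the percentages by classroom descriptively. This wording also removes the reversed gloss on integrity.

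Reconcile the number of measured students with the device and session limits (Sample Size, Physiological Outcomes and Results), so that the scheduled counts are fixed.

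Cost: one table cell and a log of scheduled and completed sessions. The criterion becomes harder to pass, since either device alone can now fail it.

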### Interpretation of Feasibility Success Criteria

Following the conclusion of the project, the success criteria will be interpreted as follows: (i) continue with large pilot/feasibility trial if all 6 success criteria are met, (ii) make minor modifications to the protocol if 3 or more criteria are met before continuing with a pilot/trial, and (iii) make significant protocol modifications if only 1 criterion is met [25].

### Physiological Measures

Classroom sitting will be measured with activPAL3 microsensors attached to the anterior right thigh as prescribed by the user manual. The outcomes of interest will include total classroom sitting time, standing time, and sit-to-stand transitions. The activPAL3 microsensor will be placed on the participants prior to the start of the school day and removed at the end of the school day before they are dismissed home. The data captured during recess times will be excluded from the data analysis. The activPAL3 microsensor has been increasingly used to objectively measure physical activity in recent years owing to its user-friendliness, practicality, and validity [30].

Postural dynamism will be measured using Noraxon Myomotion IMUs, which combine triaxial gyroscopes, accelerometers, and magnetometers. IMUs placed on the head, neck, thorax, and sacrum will be able to produce 3D kinematic and temporal outcomes, which can then be processed to produce a postural dynamism outcome.

### Sample Size

A sample size calculation was not performed as per the CONSORT extension statement for feasibility studies [25]. A classroom from a fee-paying and a nonfee-paying school will be recruited. The diversity within the sample is expected to provide a sufficiently broad spectrum of considerations to assess the feasibility of the intervention and the pragmatics of data collection. To limit the impact on the classroom environment, no more than 10 morning data collection sessions per cluster are planned. The availability of only 2 Noraxon systems and 10 activPAL sensors presents a logistical constraint that will only allow for the collection of postural dynamism data and classroom physical activity data from 20 students from each cluster respectively. The sample selected for measuring physiological outcomes will be randomly chosen from the class list. An equal number of males and females of 10 to 11-year-old students will be sampled. The participants in the qualitative study will include students who took part in physiological data collection and those who were only exposed to the intervention but did not provide physiological data.

### School Recruitment and Inclusion Criteria

Publicly funded schools will be stratified by socioeconomic categorization and then randomly contacted from a list of schools provided by the Western Cape Education Department. Only schools that have the requisite infrastructure to conduct the intervention will be considered for inclusion. This infrastructure includes technology for broadcasting the videos during normal teaching time and noninclined classroom desks. Schools that are conducting programs aimed at reducing classroom sedentariness or promoting spinal health will be excluded. At least one school from a predominantly black community will be recruited. A single class from the participant school that has students aged 10 to 11 years will be recruited into the study (Multimedia Appendix 1). Informed, written child assent and parent consent will be sought from the class teacher.

### Participant Recruitment and Inclusion Criteria

All students in the class (regardless of age) will be provided with a project information document, along with assent and parent/guardian consent forms, which will explain the methods and intervention as well as the researchers’ details. All students who return the completed assent and consent forms will be exposed to the intervention, but measurements will only be obtained from a sample of students.

### Process Evaluation

The process will be evaluated through deductive content analysis of transcribed interview data collected during qualitative in-depth interviews with the two school principals and two class teachers as well as focus group discussions with the students from each participant class. Topics related to the process of negotiating access to the classroom, impact of the experimental setup for the collection of data, acceptability of and fidelity to the intervention, impact of the intervention in the classroom, and monitoring of the implementation of the intervention will be discussed.

### Physiological Outcomes

Measurements will be taken from the study sample from each classroom at baseline and after implementation of the intervention to assess its effect. Classroom sitting will be measured for 10 consecutive school days using the activPAL3 microsensor. The sensor will be wrapped in a waterproof nitrile sleeve and attached to the proximal anterior right thigh of the participant with Hydrofilm. Participants will be required to wear the sensor from the beginning of the school day and it will be removed and collected by the researcher by the end of the school day.

### School and Participation Appreciation

As an expression of appreciation to participating schools, they will be offered up to five KUZE desks as well as the video series for ongoing use. The staff, students, and their parent/guardians will also be invited to a presentation of the relevant findings of the study.

### Data Analysis

#### Statistical Analysis

As per the CONSORT statement [25], feasibility outcomes will be described descriptively and narratively. Descriptive statistics will be used to report the clinical endpoints related to the feasibility outcomes. The number of participant classrooms and students, the number of children that remain in the study, and how many children use the school furniture throughout the study will be summarized. Owing to the small sample size, inferential statistics will most likely not be applicable. Study acceptability data will be presented per cluster as well as for the whole sample.

#### Qualitative Analysis

Thematic content analysis will be performed using Atlas.ti computer software by identifying and coding main themes and subthemes from the transcripts. A coding template will be compiled from the emerging themes and topics of interest relevant to the study objectives. An analytical diary will be kept alongside this coding template for justification of emerging themes. The coding template will be refined as more transcripts are coded. Encoded themes will be placed in context for analysis to recognize the significance and to understand the meaning thereof. Data will be analyzed per target group and by themes in cases of overlapping data between groups.

